## Results

Data collection began in fall 2021. Dissemination of the main study findings is targeted for 2024.

## Discussion

This pragmatic randomized controlled trial will assess the clinical effects of an innovative uneven-terrain treadmill in the rehabilitation of patients with LAS and CAI. We hypothesize that service members receiving uneven treadmill training will demonstrate greater improvements in clinical and instrumented measures of impairment, patient-reported function, and lower risk of injury recurrence than the control group immediately post and 18 months following treatment.

Integration of an ecologically valid activity that replicates negotiation of uneven, rocky ground commonly encountered by the military population may facilitate adaptive improvements in sensorimotor function and a return to occupation and recreational activities and may help prevent secondary injuries. Uneven-terrain treadmills present the opportunity to progressively increase the rehabilitation stimuli by incorporating tasks essential to military performance, including walking with a weapon (which obstructs the downward view of foot placement) and load carriage (which has been shown to reduce dynamic stability) [38]. Uneven-terrain treadmills also offer a relatively low-cost platform for progressive proprioceptive training, simulating real-world terrain that challenges ankle stability. The pragmatic nature of this study ensures that standard-of-care treatment is based on the specific needs of the individual patient and is consistent with the principles of evidence-based practice. This also allows for patients assigned to the intervention group to progress to more challenging rehabilitation activities on the uneven treadmill based on incremental improvements in observed findings and patient response to treatment. While a limitation to this approach is the potential for differential bias in treatment dosage, a variable that will be considered and controlled for during analysis, we view this approach to be especially salient in the evaluation of clinical effectiveness of the experimental intervention that will improve the external validity of our findings.

This clinical trial will help determine if incorporation of graded exposure on an uneven treadmill during standard rehabilitation care will lead to greater improvement in function and secondary preventive effects compared with standard rehabilitation care alone in service members with LAS or CAI up to 18 months following treatment. The incorporated patient-reported pain, kinesiophobia, physical activity, and ankle function, along with clinical and biomechanical measures, will help elucidate the clinical effectiveness of incorporation of uneven treadmill training on near- and long-term function, reinjury rates, and factors that may drive treatment outcomes. Findings from this work have the potential to directly impact the care of service members, veterans, and the broader civilian community with LAS and CAI. The findings of this study will be used to generate knowledge products that will include reports, clinician and patient education materials, and presentations that will be provided to MHS clinicians, leaders, and policy makers. In addition, the findings of this study will be promulgated as peer-reviewed conference abstracts and journal manuscript submissions.

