### Intervention

#### Overview

Once consented and enrolled, participants will be randomly assigned to either the experimental or control arm at each site using a concealed, random blocked sequence. Stratified randomization will be used to ensure an equal number of men and women are assigned to both the control and experimental groups in the LAS and CAI strata. Group allocation information will be concealed using a password-protected electronic form that will be opened by an uninvolved research staff member and communicated to the treating clinician. Both experimental and control groups will be provided standard rehabilitation care—treatment that is guided by the recent revision of the clinical practice guideline promulgated by the Academy of Orthopaedic Physical Therapy [16] on the basis of clinician experience and patient values.

Participants allocated to the experimental group will also be provided a complementary progressive treatment under the supervision of a licensed physical therapist, consisting of walking on a custom uneven-terrain treadmill (Woodway, Inc) (Figure 1) that simulates negotiation of rocky terrain (Multimedia Appendix 1) [22] for approximately 30 minutes, twice weekly, for a maximum of 12 treatments until discharge from rehabilitation. Treatment will be advanced through 3 phases of activities based on observed performance and the participant’s perceived difficulty and symptom response. Each phase will contain activities that are broadly grouped by the intensity of the proprioceptive stimulus and will be completed on the uneven treadmill. All treating physical therapists will adhere to a single training protocol to ensure standardized delivery of the uneven treadmill training across all the participating sites.

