##### Phase 3: Return to Duty and Recreational Running Tasks

The criteria for progression to this phase are met when the participant begins the transition from walking to running activities and has a FAAM ADL subscale score of >90 and FAAM Sports subscale score of >80.

Load carriage: the integration of a 12-kg load carried in a backpack (SOG Specialty Knives & Tools) will be included in phase-1 and -2 activities.Uneven trail running: integration of jogging (<2.78 m/s) and running (≥2.78 m/s) may be optionally performed in preparation for return to duty or recreational running.

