### Outcome Measures

A series of clinical, instrumented, and patient-reported outcome measures will be collected to characterize ankle-foot impairment, activity limitation, and participation restriction at baseline, during treatment, and longitudinally following treatment. Figure 2 shows the CONSORT flow diagram that details the study time points. The primary outcome of interest is improvement in patient-reported function on the FAAM. To help elucidate clinical improvement in function, we will assess if the intervention has shifted COP progression more medially during walking and if recurrence of subsequent ankle injuries has been reduced. Reinjury count data will be collected and assessed in both groups.

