### Blinding

Any research staff collecting data at any time point will be blinded to group assignment. Owing to the nature of the intervention, blinding of the participants or the clinicians providing the uneven-terrain treadmill rehabilitation intervention will not be feasible. Data analysis will be performed by researchers and statisticians blinded to group assignments.

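### The Discussion promises to control for treatment dosage, a post-randomisation variable absent from the stated models; in an efficacy model it could bias the treatment effect in either direction

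*Protocol article*

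**What the plan says.** The commitment stands in the Discussion, where individualised progression is defended and its drawback conceded: "the potential for differential bias in treatment dosage, a variable that will be considered and controlled for during analysis". No endpoint, model or method is attached to it, and dosage is not defined.

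Other sections show what kind of variable dosage is:

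- **Length (Intervention, Overview).** Treadmill training is given "twice weekly, for a maximum of 12 treatments until discharge from rehabilitation".
- **Intensity (same section).** "Treatment will be advanced through 3 phases of activities based on observed performance", together with perceived difficulty and symptoms. The Discussion adds that progression is "based on incremental improvements in observed findings and patient response to treatment".
- **Link to the outcome (Phase 3).** One condition for entry is that the participant "has a FAAM ADL subscale score of >90 and FAAM Sports subscale score of >80". Under Outcome Measures, "The primary outcome of interest is improvement in patient-reported function on the FAAM".
- **Link to arm (Overview).** "Participants allocated to the experimental group will also be provided a complementary progressive treatment", on top of the standard care that both arms receive.

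The Statistical Analysis section specifies the models without dosage. The linear mixed model and the generalised linear mixed model have Group, Time and their interaction as fixed effects. The Cox model has Group alone. The Bayesian model has six explanatory variables, none of which is dosage. Under Blinding, "Data analysis will be performed by researchers and statisticians blinded to group assignments".

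**The concern.** The trial asks whether adding treadmill training to standard rehabilitation does better than standard rehabilitation alone. The extra training is part of what is being tested, so a difference in dose between arms is not a nuisance to be removed.

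A variable that depends on both arm and prognosis should not be conditioned on when the randomised effect is estimated. Conditioning does two things. It takes out any effect that works through dose. It also compares participants who reached the same dose for different reasons, for example a slow recoverer in one arm with an average recoverer in the other, so the comparability given by randomisation is lost. If dosage includes the phase reached, the covariate is partly a function of FAAM, the primary outcome instrument.

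At stake is which of two estimates is reported as the treatment effect. They can differ in size and in sign, and the article as written supports either one.

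**Working it through.** **1. Sections side by side.** The Discussion says dosage will be controlled for. Every model in Statistical Analysis omits it. Both cannot describe the same efficacy analysis.

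**2. Trial size for the illustration.** Power and Sample Size gives 62 per group and 20% dropout: 62/(1 - 0.20) = 77.5, rounded up to 78; 4 × 78 = 312. The plan's figure reproduces. This point disputes no stated figure.

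**3. Formula.** In a linear model with Group and sessions S as covariates, least squares gives exactly

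adjusted Group estimate = unadjusted estimate - γ × Δ,

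where γ is the pooled within-arm slope of outcome on S, and Δ is the difference in mean S (experimental minus control). The two estimates agree only if γ = 0 or Δ = 0.

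All parameters below are assumptions, because the documents give no dose distribution, dose-outcome relation or FAAM SD. U is an unmeasured recovery propensity with SD 1; normal terms are given as N(mean, SD). Sessions are rounded and clipped to 1-12 in the simulations. The hand values ignore this, so they differ slightly.

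**4. Setting A: 78 per arm, 3000 replicates.** Y = τG + 5U + N(0, 5), so the SD is √(25 + 25) ≈ 7. S = 8 + sG - 1.5U + N(0, 1.5).

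γ = -(5 × 1.5)/(1.5² + 1.5²) = -7.5/4.5 = -1.67. With s = ±2 the shift is 1.67 × (±2) = ±3.3.

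| True effect | Extra sessions, experimental | Unadjusted | Dose-adjusted | Rejection, unadjusted / adjusted |
|---|---|---|---|---|
| 0 | +2 | 0.02 | +3.20 | 4.9% / 83.2% |
| 0 | -2 | 0.02 | -3.25 | 5.4% / 84.1% |
| 0 | 0 | 0.00 | -0.01 | 5.9% / 5.2% |
| 4 | +2 | 4.00 | 7.19 | 93.5% / 100% |
| 4 | -2 | 4.02 | 0.73 | 93.4% / 10.3% |

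Where the effect acts only through dose (1.5 points per session, +2 sessions, no confounding), the estimate goes from 2.90 to -0.02. Adjustment removes the effect.

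**5. Setting B: n = 200,000.** Y = τG + 6U + N(0, 8). S = 8 - 0.15(Y - 2.5) - 0.8U + bG + N(0, 2). Here sessions fall as the outcome improves.

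- Within-arm Var(Y) = 36 + 64 = 100.
- Cov(Y, S) = -0.15 × 100 - 0.8 × 6 = -19.8.
- Var(S) = 0.15² × 100 + 0.8² + 2 × 0.15 × 0.8 × 6 + 4 = 2.25 + 0.64 + 1.44 + 4 = 8.33.
- γ = -19.8/8.33 = -2.38, and Δ = b - 0.15τ.

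| True effect τ | b | Δ | By hand: τ + 2.38Δ | Simulated |
|---|---|---|---|---|
| 0 | +2 | 2 | 4.8 | +4.4 |
| 0 | -2 | -2 | -4.8 | -4.6 |
| 5 | 0 | -0.75 | 3.2 | 3.3 |
| 5 | +2 | 1.25 | 8.0 | 7.8 |
| 5 | -2 | -2.75 | -1.5 | -1.5 |

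Without sessions in the model, the true effect is recovered in each case.

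**6. If dosage means treadmill sessions.** The covariate is zero in every control. In setting A its correlation with Group is 0.94-0.97, and the SE of the Group coefficient rises from 1.13 to 3.1-4.4, that is 2.7 to 3.9 times. The coefficient then describes allocation to the treadmill with no treadmill sessions, which is an extrapolation outside the data. A column that is zero for one whole arm also identifies that arm.

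**The case against.** A reader might infer that the primary FAAM analysis, as specified, is dose-adjusted and therefore biased. The documents do not support that. The models in Statistical Analysis already compare the arms without dosage. The sentence at issue is a clause in a limitation, and it could refer to a supplementary or mediation analysis; mediators of outcome are a stated secondary aim. Such an analysis would leave the primary effect untouched. This stands: the bias arises only if the Discussion sentence is applied to the efficacy models. It does not remove the conflict, because the sentence sets no such limit.

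Second, dosage is undefined. It could mean treadmill sessions, all visits, intensity or phase. This stands too: the collinearity and unblinding points hold only for treadmill sessions, since a count of all visits need not identify the arm.

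Third, bias is not automatic. If sessions depend on prognosis alone, and neither on arm nor on the outcome, there is none: setting B without the outcome term and with b = 0 returns 5.02 for a true 5. But the Discussion itself expects dosage to be differential, and treadmill sessions are added in one arm only.

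Fourth, with treadmill sessions as covariate, setting B gives a Group coefficient of 24-30 for a true 5, and it is tempting to report that as the bias. It is the extrapolation to zero sessions. Centring sessions at the experimental-arm mean returns 5.0, so it should not be quoted as the size of the bias.

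**Conclusion.** The point holds as a conflict within the article with a real consequence. The Discussion announces control for a variable that arises after randomisation, follows response and is expected to differ by arm; the analysis section contains no such term. If the Discussion is followed in an efficacy model, the result no longer answers the trial's question. The error can go either way: about +4.4 or -4.6 for a true 0 in setting B, and in setting A a false-positive rate of 83-84% instead of about 5%, or power falling from 93% to 10%.

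These figures show what can happen, not what will. The difference of 2 visits, the dependence of sessions on recovery and the outcome SDs are assumed. No discharge criterion is given, so earlier discharge with faster recovery is a natural reading rather than a stated rule. The illustrations use a single-outcome linear model, not the trial's mixed model. Neither size nor sign can be derived from the documents.

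**What to change.** Reconcile the Discussion with Statistical Analysis:

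- State that all efficacy models compare the arms as randomised, with no dosage covariate, and replace the Discussion's promise to control for dosage accordingly.
- Define dosage (treadmill sessions, all visits, phase reached) and report it by arm descriptively.
- Confine any dose question to a supplementary causal or mediation analysis, labelled as such, with its assumptions stated and run only after the blinded primary analysis is locked. A complier-average estimate is optional and fits poorly, because sessions end at discharge rather than through non-compliance.

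The cost is a sentence or two of text. No data collection, model or sample size changes, since the models as specified already omit dosage.

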## Appendix

Multimedia Appendix 1 Supplemental video [22]. Reused under CC0 license.

Multimedia Appendix 2 Peer-review report by the U.S. Army Medical Research and Development Command - Congressionally Directed Medical Research Programs - Fiscal Year 2019 Peer Reviewed Orthopaedic Research Program - Clinical Trial Award - Funding Level 1 - Office of the Assistant Secretary of Defense for Health Affairs.

## Abbreviations

ADL: activities of daily living
CAI: chronic ankle instability
CAIT: Cumberland Ankle Instability Tool
CONSORT: Consolidated Standards of Reporting Trials
COP: center of pressure
EMG: electromyography
FAAM: Foot and Ankle Ability Measure
GLME: generalized linear mixed-effects
LAS: lateral ankle sprain
MHS: Military Health System
NPRS: numeric pain rating scale
PRECIS-2: PRagmatic Explanatory Continuum Indicator Summary
SEBT: Star Excursion Balance Test
TIDieR: Template for Intervention Description and Replication
